**Active measures*** **(from aRMT app)**					
QIDS-SR	x	x			
WSAS	x	x			x
Speech task	x		x		
Perceived sleep§	x	x			
Cognition (THINC-it app)	x			x	
**Passive measures**					
Fitbit Charge	To be worn throughout the study.				
pRMT app: GPS, acceleration, light, phone interaction, Bluetooth devices, number of contacts, battery level, weather	Will run in the background gathering data from enrolment.				
**Qualitative interview**†					x

*Weekly time spent completing questionnaires should not exceed 10 min.

†Completed once during treatment.

‡Only for the duration of treatment.

§Daily for 90 days.

ADDS, Atypical Depression Diagnostic Scale; aRMT, active RMT; AUDIT, Alcohol Use Disorder Identification Test; BIPQ, Brief Illness Perceptions Questionnaire; CTQ, Childhood Trauma Questionnaire; GAD-7, Generalized Anxiety Disorder; GSP, Global Positioning System; MINI, Mini International Neuropsychiatric Interview; PHQ-9, Patient Health Questionnaire; pRMT, passive RMT; QIDS-SR, Quick Inventory of Depressive Symptomatology-Self-Report; REDCap, Research Electronic Data Capture; RRS, Rumination Response Scale; SAPAS, Standardised Assessment of Personality: Abbreviated Scale; SRRS, Social Readjustment Rating Scale; WAI-SR, Working Alliance Inventory-Short Revised; WSAS, Work and Social Adjustment Scale.

#### Technology set-up

Participants will be asked to download four apps on their phone: RADAR passive RMT (pRMT) app, which collects background sensor data from smartphones; the RADAR active RMT (aRMT) app, which delivers clinical questionnaires; THINC-it for Remote Assessment of Disease and Relapse-Central Nervous System (RADAR-CNS), an app assessing cognitive function; and the Fitbit app. These will be linked in call to the RADAR base platform.^23^ A Fitbit Charge 3 or 4 is then delivered to them within one to two working days, at which point they are guided through the set-up. Participants will be given £10.00 for completing the enrolment session and keep the Fitbit after the study. Table 1 shows the schedule of events for the Remote Assessment of Treatment Prognosis in Depression study.

#### Follow-up

From enrolment, longitudinal collection of active and passive data begins. The current study will use the RADAR base platform and their apps to collect passive and active data, as well as a Fitbit API integration source.^23^ More information can be found at radar-base.org/.

#### Passive measures

Passive measures will be continuously gathered from smartphone sensors via the pRMT app and wearable sensors from the Fitbit. Sensor data will include Global Positioning System (GPS), acceleration, light, phone interaction (total time on phone and app usage), paired and nearby Bluetooth devices, number of saved contacts, battery level and weather. Fitbit generates digital features relating to sleep, physical activity and heart rate.

Neither the Fitbit nor the apps are validated medical tools, as they are not intended to diagnose or treat a medical condition; RADAR-based apps are purpose built for research, while the Fitbit is marketed as a fitness tracker. Despite questions surrounding the ability of digital sensors in detecting the behaviours of interest accurately, they have been found to reliably detect sleep, physical activity and location.^24–26^

No personally identifiable information will be gathered from these sensors; GPS signals are obfuscated and relative to previous location rather than exact points, and no contact details, website or app content is collected by the apps. Personal privacy is thus protected, and no identification of an individual’s home address or precise geographical location can be gathered.

#### Active measures

Participants will be asked to respond to questionnaires throughout the study period. Some of them will be delivered via the aRMT app, others will be collected via the Research Electronic Data Capture (REDCap) software,^27^ a web-based platform for research that sends email notifications to participants throughout the study.

Weekly emailed questionnaires: participants will receive weekly emails with a link to complete REDCap-delivered questionnaires, which can be complete on a smartphone or a computer. Questionnaires will be scheduled at different time intervals (fortnightly, monthly), in such a way that the maximum amount of time needed to complete them is 10 min/week.Weekly aRMT tasks: the aRMT app is designed to collect health information from research participants by sending them notifications and asking them to complete in-app tasks and questionnaires. These will include questions on depression, functionality, subjective sleep experiences and a speech task.Speech task: participants will be asked to undertake two speech tasks. The first task will require them to read out prewritten text, and the second task will ask them to answer out loud a question such as: ‘Can you describe something you are looking forward to this week?’. Participants will record their voice in quiet surroundings for both tasks via the aRMT app. Acoustic features such as pitch, jitter, shimmer, formants and intensity will be extracted.Cognition via THINC-it app: once a month, the aRMT app will notify participants that it’s time to complete the THINC-it tasks, they will be asked to open the THINC-it app to do so. THINC-it is a validated tool designed to assess cognitive function in depression.^28^ The tests incorporated in this tool—the One-Back Test, the Trail Making Test Part B, the Digit Symbol Substitution Test, Choice Reaction Time Task—assess attention, processing speed, executive function, learning and memory. The tool also incorporates the Perceived Deficits Questionnaire,^29^ a self-report questionnaire that assesses a person’s cognitive concerns.

#### End of study

Twelve weeks after participants have finished treatment, the research team will contact them to finalise their time in the study and complete endpoint assessments. In case of an unexpected change regarding their treatment, such as treatment being reduced or extended, the 3-month follow-up will commence on the day of their last core treatment session with IAPT services.

#### Extra participant contact

To maintain engagement and stay abreast of any issues, participants will be contacted after their first week after enrolment, and then in months 1, 3, 5 and 7. Researchers will initially contact participants on the phone unless an alternative method of contact is preferred and followed up with an email. Any issues raised in these calls, or sporadically reported by participants throughout the course of the study, will be recorded. Additionally, participants will be sent a monthly newsletter, via email, which will include study updates, tech tips and any frequently asked questions.

#### Post-treatment qualitative interview

In order to inform the feasibility and acceptability aims of this study, participants who complete therapy will be invited to take part in an optional qualitative interview. It will be a 30 min semistructured interview looking at participant experiences of using RMTs during psychotherapy for depression. We will invite participants to this interview once they complete treatment and will interview the first 20 who agree to take part. See online supplemental materials for a full interview schedule.

10.1136/bmjopen-2021-059258.supp1Supplementary data

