From a clinical perspective, exploring feasibility and acceptability in therapy populations can shed light on how changes in severity affect engagement with and use of digital devices, how they can be used to complement treatment and the barriers and facilitators to their use and implementation within services. From a methodological perspective, it would be important to establish the extent to which the amount and quality of data is usable and unbiased given that the added workload from therapy exercises, homework and clinical questionnaires as well as the severity of symptoms such as decreased motivation and cognitive abilities are likely to affect engagement and device use.^12^ Such studies could also inform future projects about the likely uptake in these samples in order to establish sample sizes and allocate resources.

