### Outcome measures

#### Primary outcomes

The primary outcome is to establish the feasibility of using wearable devices and smartphone sensors to monitor the behaviour of people with depression while receiving psychological treatment. Key feasibility outcomes will be related to clinical and methodological considerations, and will evaluate recruitment and participant flow, subjective reports of acceptability of methods, data availability and data quality.

The following feasibility outcomes will be reported:

Estimates of recruitment and attrition rates (figure 2).Presence and absence of passive data: ‘wear time’ for wearable devices and ‘on time’ for smartphone sensors, and the extent to which the available data allow for correlational and predictive analyses with significant statistical power.Active data availability and data quality: percentage number of tasks completed.Qualitative data: participant experience and attitudes towards data collection instruments and procedures.

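### The interviews behind the primary acceptability outcome take only therapy completers who agree early, so non-completers are left out and disengaged users are probably under-represented

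*Protocol article*

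**What the plan says.** The section on the post-treatment qualitative interview fixes two selection steps. The first is eligibility: "participants who complete therapy will be invited to take part in an optional qualitative interview". The second is order of agreement: "We will invite participants to this interview once they complete treatment and will interview the first 20 who agree to take part". The same section gives the purpose: "In order to inform the feasibility and acceptability aims of this study".

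The Primary outcomes section makes this material part of the primary outcome. Its key feasibility outcomes include "subjective reports of acceptability of methods, data availability and data quality", and the list of outcomes to be reported ends with "Qualitative data: participant experience and attitudes towards data collection instruments and procedures". Under Statistical analysis, Primary aims, the interviews are to be analysed thematically, with counts or percentages where answers can be quantified.

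Timing is stated in more than one way. The interview section places it after treatment. Table 1 marks it in the Endpoint column, and the End of study section puts endpoint assessments twelve weeks after treatment. The Table 1 footnote attached to the interview row reads "Completed once during treatment".

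**The concern.** The study exists to describe engagement and missing data in people under treatment for depression. The Introduction says that work in therapy populations can "shed light on how changes in severity affect engagement with and use of digital devices", and it expects therapy workload, low motivation and cognitive symptoms to reduce engagement. Wear time, task completion and attrition show how much data are lost. Interviews are the natural way to learn why.

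A sample that requires therapy completion, and then takes whoever agrees first, leaves out one group by rule and probably thins out another. Order of agreement also favours people who enrolled early or had shorter treatment. That could concentrate the interviews in one phase of the pandemic, which the Discussion says is likely to affect attitudes to technology.

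At stake is the reading of the acceptability result. Percentages from these interviews, reported without a qualifier, could be taken to describe the cohort. Once the 20 places are filled, no analysis can recover the missing views.

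**Working it through.** **The plan's own figures.** The number 20 has no stated derivation, so there is nothing to reproduce for the interviews. The cohort size does reproduce. For r = 0.39, two-sided alpha 0.05 (the article does not state sidedness) and power 0.80, the Fisher z formula n = ((1.960 + 0.842) / atanh(0.39))² + 3 gives 49.3, so 50. Inflating for 20% attrition, 50 / 0.80 = 62.5, so 63, against a stated target of 65. None of this depends on the interview rule.

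**Share interviewed.** 20 / 65 = 31% of those recruited.

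**What the rule does to non-completers.** Let k be the number of the 65 who do not complete therapy. Under the stated rule the expected number among interviewees is 0. A random draw of 20 from all 65 would contain 20 × k / 65 on average. The article gives no non-completion rate, so k is assumed over a range:

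| Assumed non-completion | k | Expected in a random 20 | Under the stated rule |
|---|---|---|---|
| 10% | 6 | 120 / 65 = 1.8 | 0 |
| 20% | 13 | 260 / 65 = 4.0 | 0 |
| 50% | 32 | 640 / 65 = 9.8 | 0 |

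At the assumed 20%, the chance that a random 20 contains no non-completer is C(52,20) / C(65,20) = 0.4%. So in most of this range the absence comes from the rule and not from chance. At 10% that chance is about 10%.

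**Why no bias figure follows.** Write q for the non-completion rate, and a₁ and a₀ for acceptability among completers and non-completers. Cohort acceptability is (1 − q)a₁ + q·a₀. A sample that represented completers would give a₁, so the difference is q(a₁ − a₀). The article supplies none of the three quantities. The sign is positive only if completers find the methods more acceptable, which is plausible but not shown. Order-of-agreement selection within completers adds a second term that cannot be written down from the article.

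**Timing, side by side.** Interview section: once treatment is complete. Table 1 column with the End of study section: twelve weeks after treatment. Table 1 footnote: during treatment. These cannot all hold. The footnote mark is shared with the working-alliance row, so it may have been meant for that row, but the article does not say so.

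**The case against.** Completing therapy is not the same as succeeding with the devices. A completer who stopped wearing the tracker or ignored the app can still be interviewed, and someone who left therapy may have used the devices well. A reader might infer that the plan excludes everyone for whom the methods failed. The text does not support that: it excludes therapy non-completers, and under-representation of disengaged completers is a probable result of early-agreement selection, not a stated rule.

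The interview is also not the only evidence. Participants are contacted after the first week and in months 1, 3, 5 and 7, and "Any issues raised in these calls, or sporadically reported by participants throughout the course of the study, will be recorded". These reports carry no therapy-completion condition and are summarised under the primary aims. Attrition, wear time and task completion are primary outcomes too, and the secondary analysis asks whether clinical data predict attrition or missing data.

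Finally, this is an optional thematic interview. No acceptability percentage is defined as an endpoint, and no test depends on it.

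All of this stands and limits the point. It does not remove it. An issue log records problems as they arise and does not explore experience and attitudes in a structured way. The article describes no exit interview for people who stop therapy or withdraw.

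**Conclusion.** The point holds in a limited form, as a worthwhile low-cost improvement. Interview-based acceptability excludes therapy non-completers by rule and probably under-represents disengaged users. The likely direction is overstatement, on the assumption that those left out find the methods less acceptable. The size cannot be derived from the article.

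Two stronger readings are tempting and should be resisted. A reader might take 20% of 65, that is 13 people, as having no chance of interview. The 20% is potential study attrition used to inflate the sample size and is not stated to be therapy non-completion. Invitations go out when treatment ends, twelve weeks before the end of study, so some of those lost could already have been invited. The article also does not define therapy completion, and it allows for treatment being shortened. A reader might likewise attach a bias in percentage points, but that needs acceptability and non-completion rates that the article does not give.

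The conflict over interview timing is real, and correcting it is a small edit.

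**What to change.** 1. Keep 20 interviews, but extend the invitation to participants who stop therapy or leave the study, where their consent allows contact.
2. Replace first-to-agree selection with purposive sampling by engagement, using wear time and task completion. Hold places for low-engagement and non-completing participants, and release unfilled ones after a set time.
3. Report any counts or percentages by therapy-completion and engagement group.
4. If non-completers cannot be reached, limit the acceptability conclusion to therapy completers and say so among the limitations.
5. Reconcile the interview section with the Table 1 column and footnote on timing.

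The number of interviews is unchanged. The cost is a protocol amendment and slower recruitment of low-engagement participants, with some held places likely to revert to others. Whether withdrawn participants may be contacted again cannot be judged from the article and should be checked against the consent terms first.

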### Outcome measures

#### Primary outcomes

The primary outcome is to establish the feasibility of using wearable devices and smartphone sensors to monitor the behaviour of people with depression while receiving psychological treatment. Key feasibility outcomes will be related to clinical and methodological considerations, and will evaluate recruitment and participant flow, subjective reports of acceptability of methods, data availability and data quality.

The following feasibility outcomes will be reported:

Estimates of recruitment and attrition rates (figure 2).Presence and absence of passive data: ‘wear time’ for wearable devices and ‘on time’ for smartphone sensors, and the extent to which the available data allow for correlational and predictive analyses with significant statistical power.Active data availability and data quality: percentage number of tasks completed.Qualitative data: participant experience and attitudes towards data collection instruments and procedures.

**Figure 2 F2:**
[figure not shown]
Participant flow in the Remote Assessment of Treatment Prognosis in Depression (RAPID) study.

#### Secondary outcomes

Secondary outcomes will evaluate the relationship between digital data and clinical outcome measures, both at individual time points and as prognostic factors for recovery after treatment. Scores on clinical scales will be used in addition to individual symptom domains.

Digital outcomes will be derived from smartphone and Fitbit sensors, and digital features from passive measures described in the ‘Passive Measures’ section, such as GPS signal patterns, sleep, phone use and Bluetooth interactions. They will be extracted to form averages that encapsulate daily, weekly and within-treatment means and SDs or frequency counts.

Clinical state will be measured using:

Patient Health Questionnaire (PHQ-9)^30^: the nine-item questionnaire that is widely used for measuring depression in IAPT services.Generalized Anxiety Disorder^31^ questionnaire: will be measured as it gathers important anxiety symptoms which are so often comorbid with depression.Quick Inventory of Depressive Symptomatology-Self-Report (QIDS-SR)^32^: this is a 16-item inventory of depression for patients who identify as depressed or who may be suffering from depression.Work and Social Adjustment Scale^33^: a measure of quality of life/disability, which is a five-item assessment of perceived social and work-related functional impairment used widely across a range of mental and physical disorders.Cognition via the THINC-it app.

Participants will be considered to be in remission if they have experienced a reduction of at least 50% in depressive symptomatology from the start of treatment, or no longer meet criteria for depression according to the PHQ-9 (scoring below the cut-off of 5). Subdimensions of depression—for example, interest in activities, motivation, appetite—will be gathered from the QIDS-SR.

The sociodemographic, clinical and contextual variables measured, such as illness severity, cognitive function and social support, will be taken as covariates.

Standardised Assessment of Personality: Abbreviated Scale^34^: an eight-item personality test that screens for personality disorder.Brief Illness Perceptions Questionnaire^35^: provides an insight into the participant’s views about their underlying condition and how well they see themselves coping with it.Life Stress Scale (Social Readjustment Rating Scale)^36^: this is a retrospective questionnaire for identifying major stressful life events.Childhood Trauma Questionnaire^37^: a 26-item scale that assesses five types of maltreatment: sexual abuse, physical abuse, emotional neglect, physical neglect and emotional abuse.Alcohol Use Disorder Identification Test^38^: widely used scale in primary care that measures alcohol consumption, drinking behaviours, and identifies harmful alcohol use.Oslo 3-item Social Support Scale^39^: a brief instrument that assesses social support.Perceived Stress Scale^40^: a measure of the degree to which situations in one’s life are appraised as stressful. Items were designed to assess how unpredictable, uncontrollable and overloaded respondents find their lives to be.Working Alliance Inventory-Short Revised^41^: a 12-item scale measuring therapeutic alliance on three key components: (a) agreement on the tasks of therapy, (b) agreement on the goals of therapy, and (c) development of an affective bond.Rumination Response Scale^42^: a 10-item scale that measures rumination.COVID-19-related questions: isolation status and their perceived effect, confirmed or suspected diagnosis of COVID-19 as well as social distancing practices.Treatment status: questions on whether psychotherapy has begun, whether they take concomitant medication and adherence (eg, ‘Are you taking medication for your mental health? If so, which one?’ or ‘Have you missed any psychotherapy sessions this week?’) and the broad content of their therapy sessions.

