#### Inclusion criteria

Adults with a current depressive episode as measured by the Mini International Neuropsychiatric Interview (MINI^19^).Being on the waiting list to receive treatment for depression at IAPT services, with an expected wait of at least 7 days (to a maximum of 5 weeks) between scheduled enrolment and first treatment session. Due to the prevalent comorbidity with anxiety disorders, people with a main diagnosis of anxiety were also included, provided they met inclusion criterion A.Existing ownership of Android smartphone with sufficient memory space for the relevant apps.Able and willing to use a wrist-worn device for duration of the study.Able to give informed consent for participation.Sufficient English language skills to understand consent process and questionnaires.

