### Secondary aims

Digital features that account for sleep, activity, sociability and cognition will be extracted from sensor data and correlated against scores on scales of depression, anxiety and functionality. Feature extraction will replicate the methods used by the RADAR-CNS consortium.^23 44^ Regression or classification analyses will be carried out for clinical scores to see whether higher impairment is associated with behavioural features. Regression and classification approaches will also be used to determine whether clinical data predict subject attrition or missing data patterns.

We will carry out univariate and multivariate associations on digital features and clinical state, as well as within and between individual comparisons. In order to unearth digital profiles in the sample, individuals will be clustered together based on their response patterns using latent class analysis. This person-centred approach will unpick some of the heterogeneity in the sample and assumes there are underlying latent variables that underpin distinct symptom profiles,^45^ and has been used extensively in the construction of the subtypes of depression.^46^ This model will aid in the description of longitudinal behavioural patterns in this sample.

To evaluate the prognostic value of digital features, we will use machine learning methods on the extracted aggregated features and clinical information, provided there are sufficient data points. A multivariate prediction model will be constructed, and different feature selection algorithms will be applied. Model performance will be evaluated through cross-validation, putting stress on sensitivity and specificity of relapse prediction model. We will also use dynamic structural equation modelling to evaluate the lagged associations across study time points.

Where data are missing at random and assuming it is not significantly high, multiple imputation methods will be carried out. If missing data are high, this may be incorporated into the model as a predictor, or otherwise used informatively.

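### The prognostic model has no predictor cut-off and its inputs include within-treatment averages, so a feature that only mirrors current mood can look prognostic

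*Protocol article*

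**What the plan says.** All references are to the protocol article.

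- **Feature windows (Secondary outcomes).** Of the sensor-derived features: "They will be extracted to form averages that encapsulate daily, weekly and within-treatment means and SDs or frequency counts". Three windows are named, and the within-treatment one is the only window longer than a week.
- **Uses (Secondary outcomes).** The relation of digital data to clinical outcome is to be evaluated "both at individual time points and as prognostic factors for recovery after treatment". One feature set has two uses.
- **Outcome (Secondary outcomes).** Remission is a "reduction of at least 50% in depressive symptomatology from the start of treatment", or a PHQ-9 score below 5. No assessment time is attached.
- **Model (Statistical analysis, Secondary aims).** For prognosis, "we will use machine learning methods on the extracted aggregated features and clinical information, provided there are sufficient data points". Performance is judged by cross-validation, and the text there names relapse, not recovery, as what the model predicts.
- **Time-ordered analysis (same section).** "We will also use dynamic structural equation modelling to evaluate the lagged associations across study time points".
- **Available time line.** Patients enter "with an expected wait of at least 7 days (to a maximum of 5 weeks) between scheduled enrolment and first treatment session" (Inclusion criteria). Sensor data start at enrolment (Follow-up), and endpoint assessments come 12 weeks after treatment finishes (End of study).

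**The concern.** A prognostic factor has to be known before the outcome it predicts. A mean or SD taken over the whole of therapy covers the same weeks in which a fall from the start of treatment accrues. If a patient who is improving sleeps, moves or uses the phone differently in the later weeks, that change is already inside the predictor. Nothing restricts the daily and weekly summaries to an early period either.

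The secondary aim is to learn whether digital signals have prognostic value in psychological treatment, and the Introduction motivates this by tailoring treatment. A whole-treatment average is complete only when therapy ends, so it could not guide that therapy, and it cannot separate a marker of present mood from a forward predictor. Cross-validation does not expose the problem, because the overlap is present in every fold.

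**Working it through.** **1. The plan's own figure.** Sample size section: r = 0.39, significance level 0.05, type 2 error 0.20, n = 50. By Fisher's z, two-sided:

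n = ((1.960 + 0.842) / atanh(0.39))² + 3 = (2.802 / 0.412)² + 3 = 49.3, rounded up to 50.

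This reproduces. Attrition: 50 / 0.80 = 62.5, so 63, against the stated 65 (65 × 0.80 = 52). The sample size is not in question. I use r = 0.39 below as the strength of the concurrent correlation.

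**2. Time windows side by side.**

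| Item | Period covered |
|---|---|
| Waiting-period data | enrolment to first session, expected 7 days to 5 weeks |
| Within-treatment mean and SD | first to last session |
| Symptom fall that defines remission | begins at start of treatment; end not stated |
| Endpoint visit | 12 weeks after treatment; not tied to remission in the text |

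Rows 2 and 3 overlap from the first session onward.

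**3. Simulation A: a feature with no forward information.** Assumed, not in the documents: 3 waiting weeks; 12 treatment weeks; baseline score mean 16, SD 4.5; fractional drop with mean 0.45, SD 0.30, independent of baseline; 200,000 patients.

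- severity(t) = baseline × (1 − drop × t/12)
- feature(t) = r × z(severity(t)) + √(1 − r²) × residual, with 50% or 80% of the residual variance a stable person effect
- remission = drop of at least 0.50, so the proportion is 1 − Φ((0.50 − 0.45)/0.30) = 0.43

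| AUC for remission | r = 0.30 | r = 0.39 | r = 0.50 |
|---|---|---|---|
| Waiting-period mean | 0.50 | 0.50 | 0.50 |
| First 3 treatment weeks | 0.52–0.53 | 0.53–0.54 | 0.54 |
| Whole-treatment mean | 0.58–0.59 | 0.60–0.62 | 0.63–0.65 |

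Each range spans the 80% and 50% stable components.

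**4. Simulation B: different assumptions and a later outcome.** Assumed: 3 waiting, 16 treatment and 12 follow-up weeks; baseline mean 16, SD 4.5; change mean −7, SD 5, independent of baseline; weekly autocorrelated noise; remission by either arm of the definition; r = 0.39; 100,000 patients. Partial r is the correlation of the feature with outcome severity given baseline severity.

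| Feature window | End of treatment: partial r; AUC | 12 weeks after: partial r; AUC |
|---|---|---|
| Waiting period | 0.02; 0.54 | 0.02; 0.54 |
| First 4 weeks | 0.09; 0.57 | 0.09; 0.57 |
| Whole treatment | 0.26; 0.64 | 0.23; 0.63 |
| Last 4 weeks | 0.37; 0.69 | 0.31; 0.66 |

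For concurrent correlations from 0.30 to 0.80, the whole-treatment partial r runs from 0.20 to 0.60 at end of treatment and from 0.18 to 0.55 at 12 weeks, against 0.02 to 0.06 for the waiting period.

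**5. Reading.** Apparent prognostic value rises as the feature window moves later, although the feature carries nothing beyond current mood. Baseline adjustment does not remove it. A post-treatment outcome shrinks it only somewhat, because improvement already achieved carries forward.

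**The case against.** **The within-treatment mean is one of three windows.** This stands. A reader might infer that the prognostic features are averaged over the whole of treatment and nothing else. The text does not say so: daily and weekly summaries are also formed, and since sensors run from enrolment they cover the wait. The gap is that no window is assigned to the prognostic model, so the within-treatment summaries enter with the rest.

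**The outcome may be measured after treatment.** The article speaks of recovery after treatment, and PHQ-9 is on the endpoint schedule. If remission is read there, within-treatment features do precede it. This stands in part: the text does not tie remission to that visit, and simulation B shows the effect is reduced, not removed.

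**There are mitigations.** Lagged dynamic structural equation modelling is planned, clinical information enters the model, illness severity is a covariate, and the Reporting standards section promises full feature definitions. These make it wrong to say that a concurrent marker will be reported as prognostic. But the lagged model is an additional analysis, and none of these sets a cut-off for the machine-learning model.

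**The size is modest for this sample.** With n = 50 and 43% events (21.5 against 28.5), the Hanley–McNeil standard error at AUC 0.62 is 0.081, giving 0.62 ± 1.96 × 0.081, or 0.46 to 0.78. One study would often not tell this from 0.50. That stands as a limit on size; it does not make the estimate interpretable as prognosis. AUCs of about 0.7 or more can be had by contrasting the treatment mean with the waiting-period value, but the article specifies no such contrast, so I do not rely on them.

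**Windows belong in an analysis plan.** A full plan may well settle this. The point does not rest on silence alone: the article itself names the windows, sends that feature set to prognosis, and counts remission from the start of treatment.

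**Conclusion.** The concern holds in a limited form. The article passes within-treatment means and SDs, with daily and weekly summaries, to the prognostic analysis without a predictor cut-off, and does not say when remission is assessed. Predictor and outcome periods can overlap, so a feature that only mirrors current mood can look prognostic.

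At r = 0.39 the whole-treatment mean gives an AUC of about 0.60 to 0.62 where the waiting period gives 0.50 (simulation A). Simulation B gives 0.64 against 0.54, or 0.63 against 0.54 with the outcome 12 weeks after treatment. Therapy length, the size and shape of the decline and the noise structure are my assumptions. The direction is the same in both models; the size depends on the concurrent correlation, the window finally used and whether current severity is adjusted for.

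A reader might conclude that this undermines the study. It does not. The model is a secondary, exploratory analysis, run only if the data suffice, and the descriptive feasibility outcomes and the sample size are untouched. It is worth correcting before the model is fitted.

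**What to change.** In Secondary outcomes and in the Secondary aims analysis:

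1. Set a landmark for the prognostic model and use only features from before it: the waiting period alone, or the waiting period plus a pre-specified early-treatment window, adjusting for PHQ-9 at the landmark.
2. State that remission is assessed at the 12-week post-treatment endpoint.
3. Reconcile recovery (Secondary outcomes) with relapse (Secondary aims) as the prediction target.
4. Report whole-treatment means and SDs as concurrent associations, or as predictors only of outcomes after treatment ends, with adjustment for end-of-treatment PHQ-9.

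**Cost.** Wording only; the schedule already provides for the data and the sample size does not change. Shorter windows are noisier. The wait may be only 7 days and the Fitbit is delivered one to two working days after enrolment, so waiting-period wearable features may rest on few days; this is a reason to allow the early-window model. Reported sensitivity and specificity will probably be lower.
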